**Methods:**

We proposed a mixed method study among MSM in Ghana. First, we will develop the intervention protocol using the Convergence Framework, which combines three interventions that were previously implemented separately in Ghana for reducing stigma at the HCF-level, increasing HIV testing at the peer group-level, and increasing peer social support at the individual-level. Then, we will conduct a cluster randomized controlled trial with four pairs of HCFs matched on staff size. HCFs within each pair are randomized to the HCF-level stigma-reduction intervention or control arm. MSM (n = 216) will be randomized to receive the group-level and individual-level interventions or standard of care control arm. MSM will be assigned to receive HIV testing at one of the HCFs that match their study assignment (intervention or control facility). The frequency of HIV testing between MSM in the study arms at 3 and 6 months will be compared, and the predictors of HIV testing uptake at the HCF, peer group and individual-levels will be assessed using multi-level regression models.

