### Study participants

#### HCF staff

The study sample will consist of staff from HCFs in Ghana (n = 290; 90 in formative phase; 200 in RCT phase). We expect that the HCF staff sample will be predominantly composed of cisgender women (75%) based on our previous work in HCFs which show that women represent the majority of HCF staff. Although the health facility stigma-reduction intervention will be provided to a minimum of 70% of HCF staff in each facility, we will collect baseline and follow-up data on a random sample of 200 HCF staff in the RCT phase.

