#### Step 8 (Test)

We will conduct an RCT of the multi-level intervention with a 6-month wait-list control. In each city, we will create two pairs from the 4 HCF sites matched by the number of HIV tests performed in the calendar year 2020. We will randomly assign clinics (enveloped odd/even) within each pair to either receive the HP+ or the wait-list control. MSM will be randomly assigned to receive either Nyansapo and HIVE^3^ or wait-list control. MSM in the intervention group will be asked to follow-up for HIV testing and services at one of the HCFs assigned to the HP+ intervention and the MSM in the wait-list control group will be asked to follow-up at any of the HCFs in wait-list control. Nurses from the intervention HCFs will participate as guest facilitators in one of the Nyansapo sessions and will use that opportunity to reach out to MSM to visit their facility for testing. Our primary hypothesis is that the multi-level intervention will increase uptake of HIV testing among MSM participants. We will use research data collectors to measure frequency of HIV testing among MSM at 3- and 6-months post-intervention using a combination of self-report survey and verification by study nurses (for men who get tested for HIV at participating HCFs.) Our secondary hypothesis is that the multi-level intervention will reduce intersectional stigma that HCF staff convey and that MSM experience in HCFs. We will use research data collectors to administer a survey measuring intersectional stigma 1) in the HCFs at baseline, 3-months post and 6-months post intervention and 2) among MSM at baseline, 3- and 6-months post intervention.

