### Sample size

Sample size calculation for MSM participants is based on testing the primary study hypothesis that multi-level intervention will increase the HIV testing rate. Our previous study showed that the 6-month HIV testing rate among MSM was 40%. We hypothesize that this rate will increase to 70% after six months of multi-level intervention. This estimate is based on the evidence from the 3MV trial which showed 81% greater odds of HIV testing in intervention compared to the control group at 6-months and is conservative in comparison to UNAIDS “90-90-90” goals. To determine whether our estimated rate of 70% following interventions is different than the comparison rate of 40% with 80% power and Type I error probability 0.05, while assuming a 10% intra-cluster correlation coefficient, we need 86 MSM participants in each arm, or 172 in two arms by the end of 6-month follow-up. Given a cohort retention rate of 80% (based on retention in previous studies with MSM in Ghana), a total of 216 MSM will be recruited. To evaluate the impact of intervention training on intersectional stigma among staff, we will test whether the training intervention will increase the willingness of HCF staff to provide services to MSM. The historical data shows that the willingness rate is 75%. We expect that the intervention will increase the willingness rate up to at least 90% in the intervention clinic staff, while there is no change in the control group, and we will need 97 staff in each arm, or 194 in total, to achieve 80% power with a 5% Type I error rate.

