Additionally, multivariable logistic regression will be used to compute the adjusted odds ratio and 95% CI for the binary outcome–HIV testing. The successful uptake of HIV testing can be dependent on the environment in the HCF so that HIV testing among MSM participants at the same HCF may be corrected or “clustered.” To account for the potential post-randomization clustering effect in this individually randomized clinical trial, a generalized linear mixed-effects model with a logit link function will be fitted, and this model includes both HCF cluster-level and MSM individual-level factors. Structural equation modeling will be performed to evaluate the association between the multilevel intervention and uptake of HIV testing while simultaneously assessing the mediation role of intersectional stigma. We will also perform the same analyses for HIV testing within three months of randomization, although the analyses may be underpowered. The likelihood of intervention contamination across the study groups could not be excluded, because some participants may not receive the respective interventions to which they are randomized, e.g., some members of the control group may seek health care at the intervention HCFs during this trial. Therefore, we will also perform per-protocol analysis, which includes only those participants who strictly adhere to the protocol and report the results along with the results of the intention-to-treat analyses. To estimate the effect size of the HP+ intervention for staff, we will compare the rates of willingness to provide healthcare to MSM between the staff in intervention and control HCFs. Chi-square test and t-test will be used for the binary (willingness) and continuous (stigma score) outcomes, respectively. Multivariate logistic or linear regression models will be fitted while adjusting for confounding factors such as sex and job title of the staff.

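### The staff comparison is sized and tested as if staff were individually randomised, although HP+ is allocated to four facilities against four, so the stated 80% power and 5% error rate hold only at zero staff intra-cluster correlation

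*Protocol article*

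**What the plan says.** Allocation: the Abstract describes a "cluster randomized controlled trial with four pairs of HCFs matched on staff size". Step 8 (Test) states: "We will randomly assign clinics (enveloped odd/even) within each pair to either receive the HP+ or the wait-list control". With four pairs, there are four facilities per arm.

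Staff sample: under Study participants, HCF staff, "we will collect baseline and follow-up data on a random sample of 200 HCF staff in the RCT phase".

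Staff sample size: "The historical data shows that the willingness rate is 75" per cent, and "We expect that the intervention will increase the willingness rate up to at least 90% in the intervention clinic staff", with no change in control. From this, "we will need 97 staff in each arm, or 194 in total, to achieve 80% power with a 5% Type I error rate". No ICC, design effect or number of facilities enters this sentence. The MSM calculation in the same section assumes an ICC of 10%.

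Staff analysis, in the Statistical analysis plan section: "Chi-square test and t-test will be used for the binary (willingness) and continuous (stigma score) outcomes, respectively". Logistic or linear regression follows, adjusted for factors such as sex and job title. The mixed-effects model for clustering by facility in that section is written for HIV testing among MSM, not for staff outcomes.

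**The concern.** Staff in one facility share managers, working norms and, in the intervention arm, the same training groups and champions. Their answers on willingness and stigma are therefore likely to be correlated. Because the facility is the unit allocated, that correlation adds directly to the variance of the difference between arms. A test that counts 100 independent staff per arm, when there are four allocated units per arm, understates this variance.

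The trial does allow for an ICC, but in the MSM part, which the analysis section itself describes as individually randomised. In the staff part, where allocation is by facility, there is no allowance.

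At stake are the error rate of the staff willingness and stigma-score comparisons and the width of the interval around the HP+ effect. The second matters most here, because Aim 2 is to supply effect sizes for planning a definitive trial.

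**Working it through.** **Inputs.** From Sample size: p0 = 0.75, p1 = 0.90, power 0.80, alpha 0.05 (sidedness not stated; two-sided reproduces the figure). From the Abstract and Step 8: k = 4 facilities per arm. From Study participants: 200 staff, so m = 200/8 = 25 per facility (equal split assumed). The staff ICC is not in the document. The range 0.01 to 0.10 is an assumption; its upper end is the value the article uses for MSM.

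**1. The plan's own figure.** Unpooled two-proportion formula without clustering:

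n = (1.960 + 0.842)² × (0.75×0.25 + 0.90×0.10) / 0.15² = 96.8, rounded up to 97 per arm.

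This matches exactly, so 97 contains no design effect. (The pooled-variance form gives 100.)

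**2. Planned chi-square test under clustering.** Design effect DE = 1 + (m − 1) × ICC = 1 + 24 × ICC. The true type I error of the unadjusted test is 2 × [1 − Φ(1.96/√DE)]. The unadjusted interval is too narrow by √DE.

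| Assumed ICC | DE | Type I error | Interval too narrow by |
|---|---|---|---|
| 0 | 1.00 | 5.0% | 1.0 |
| 0.01 | 1.24 | 7.8% | 1.11 |
| 0.05 | 2.20 | 18.6% | 1.48 |
| 0.10 | 3.40 | 28.8% | 1.84 |

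Beta-binomial simulation (4 versus 4 facilities, 25 staff each) gives about 8%, 19% and 29% at the three non-zero values.

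**3. Power of a valid facility-level test.** This is a different test from the one planned. The noncentrality is 0.15 / √(0.2775 × DE / 100), where 0.2775 = 0.75×0.25 + 0.90×0.10. It is referred to a t distribution with 6 df (eight facility means, unpaired) or 3 df (four pairs, if matching gains nothing).

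| Assumed ICC | Noncentrality | Power, 6 df | Power, 3 df |
|---|---|---|---|
| 0 | 2.85 | 66% | 49% |
| 0.01 | 2.56 | 57% | 42% |
| 0.05 | 1.92 | 37% | 27% |
| 0.10 | 1.54 | 26% | 19% |

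Simulation agrees to about one percentage point (58%, 38% and 26% for 6 df).

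**4. How much is the ICC and how much the number of facilities.** With 100 per arm, zero ICC and the normal approximation, power is 81%. Moving to 6 df alone takes it to 66%. At ICC 0.01 the normal approximation gives 72%, against 57% with 6 df. At low ICC the small number of facilities therefore costs more than the correlation does.

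**5. More staff would not cure it.** With four facilities per arm, the effective sample size per arm cannot exceed 4/ICC. Requiring 4/ICC ≥ 96.8 gives ICC ≤ 0.041. Above that, 80% power is out of reach at any number of staff, even under the normal approximation.

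**The case against.** The staff outcome is secondary. The trial is framed around feasibility and effect size, and the analysis section introduces the staff comparison as estimation of an effect size. No confirmatory decision rests on it, and the size of the error depends on an ICC that the article does not give. This stands and limits the seriousness. It does not remove the point, because the Sample size section says that a hypothesis will be tested and attaches an explicit power and error rate. An interval that ignores clustering also misinforms the next trial.

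Four stronger readings are tempting but not supported:

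- A reader might infer that the planned test is both too liberal and badly underpowered. The inflated error belongs to the planned chi-square test; the low power belongs to a valid facility-level test. In simulation the planned test still rejects about 70% to 79% of the time under 75% versus 90%, but at an error rate above 5%, so this is not valid power.
- A reader might set the 200 staff against the 194 required and conclude that too little is allowed for loss. The article gives no staff retention rate; its 80% comes from earlier MSM studies. Staff who expect to leave are excluded, staff surveys are anonymous, and the article does not say that the same individuals are resurveyed. An attrition claim cannot be built on this.
- A reader might say that the staff baseline survey is not used. The Statistical analysis plan provides a difference-in-differences analysis if the groups prove non-equivalent at baseline. That use is conditional and does not adjust for clustering, but baseline data are not ignored.
- A reader might extend the point to the whole secondary hypothesis. That hypothesis also covers stigma experienced by MSM, which these staff tests do not touch.

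Pair matching or baseline adjustment could recover some precision. Neither appears in the staff calculation or the named staff tests, and both use up degrees of freedom that are scarce with eight facilities.

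**Conclusion.** The point holds for the staff comparisons of willingness and stigma score. The figure of 97 per arm is arithmetically right for individually randomised staff and wrong for facilities allocated four against four. The stated 80% power and 5% error rate hold only if the staff ICC is zero.

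The binary-outcome figures above rest on an assumed ICC of 0.01 to 0.10, 25 staff in every facility, and no gain from matching or baseline adjustment. A different ICC changes the size of the problem but not its direction. The t-test on the stigma score has the same defect; its size would depend on that outcome's own ICC.

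This should be fixed. It is not critical to the trial, because it affects the staff half of a secondary hypothesis and leaves the primary MSM outcome untouched.

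**What to change.** 1. In the Statistical analysis plan section, replace the staff chi-square test, t-test and ordinary regression with an analysis that respects the allocation: either a comparison of facility-level summaries, or a mixed model with a facility random intercept and small-sample degrees of freedom.
2. State whether the matched pairs are kept in that analysis (3 df for a paired test, 6 df for an unpaired one). The Abstract and Step 8 name different matching variables (staff size; number of HIV tests in 2020), and this should be settled at the same time.
3. If facility baseline means are adjusted for, limit the adjustment to what eight facilities can support and state the remaining degrees of freedom. Each facility-level covariate costs one.
4. In Sample size, replace the 80%/5% statement with the power of 200 staff in eight facilities over a stated ICC range under the chosen analysis. Alternatively, present the staff comparison as estimation only, with cluster-adjusted intervals and the observed ICC reported for the next trial.

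The cost is a change of wording and a less favourable stated power. No extra staff or facilities are needed. The employing facility is already to be recorded for HCF staff (Confidentiality and security of data), so the facility-level analysis should need no new data.

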### Recruitment

This study involves two phases (formative phase and randomized controlled trial phase) and two target population groups: HCF staff and MSM. There are specific criteria for recruitment for each population group in each of the study phases. The investigative team is partnered with three Ghanaian civil society organizations who will implement the research activities in their respective geographic regions and target populations. Two are MSM-led organizations that have worked with the team on previous studies. Both organizations have a track record in recruitment and retention of MSM in research studies. The third organization is a Ghanaian NGO that provides research and intervention implementation technical assistance services in Ghana, including for stigma-reduction intervention research, and brings strong relationships with the health sector in Ghana.

#### HCF staff

Recruitment for the intervention will target training a minimum of 70% of HCF staff who will encounter MSM seeking HIV testing at the facility (e.g., nurses, lab staff, guards, receptionists) and key staff (influencers) from different cadres of staff in other departments where MSM may need to seek health services (e.g., outpatient department, men’s in-patient ward, genitourinary, emergency). We will recruit staff that represent a diverse cross-section of the facility who MSM are likely to encounter during the process of HIV testing (e.g., receptionist, security guard, nurse, HIV counselor, cashier). We will secure an updated list of HCF staff (HCFs already provided a list of staff by category in support of the proposal) and construct a random sample that will be contacted from the list, while allowing for staff to confidentially decline participation. For the formative research, each FGD will include 6–8 persons stratified by medical versus non-medical staff. We will also conduct IDIs with HP+ HCF staff and client trainers (n = 10) who were trained as facilitators under our previous work and who have been delivering the HCF HP+ intervention to HCFs in Ghana not involved in our proposed study.

#### MSM

We will recruit MSM using Starfish sampling—a combination or venue-based/time location sampling and peer-referral sampling strategies [59]. We have used both recruitment strategies separately in previous studies; however, recent evidence demonstrates that the Starfish Sampling (combining the two strategies) optimizes the recruitment of yield of populations that are considered hidden. We will conduct face-to-face recruitment through our civil-society partners serving MSM in-house programs and outreach activities. We will also recruit using coupon-based peer-referrals, which are a component of respondent driven sampling (RDS) [60–62]; however, our interest is in recruiting a sufficient sample size of MSM; therefore, we will not apply statistical weights to attempt to generate a population estimate that is the hallmark of the RDS approach. We established region-specific enrollment targets [Accra (n = 108), Ashanti (n = 108)] based on estimation of MSM population sizes in each city. We will employ and train research assistants from outreach staff at our two civil society organizations who already have extensive experience engaging MSM for research and program activities.

### Statistical analysis plan

The intervention outcomes will be assessed using a rigorous intention-to-treat approach where participants are included in the analysis as assigned initially, regardless of whether they receive the multi-level intervention or usual care. First, we will compare baseline data to see if randomization made the groups equivalent. If we determine non-equivalence, then the non-equivalent variables will be accounted for in the final analyses using a difference in differences analytic technique where randomization is used to minimize any perception of bias in the selection of sites by investigators. We will determine the proportions of HIV testing at 3- and 6-month follow-up assessments among MSM with 95% confidence intervals (CI). To test the primary study hypothesis that multi-level intervention will increase the uptake of HIV testing within six months of randomization, we will use an uncorrected chi-square statistic.

Additionally, multivariable logistic regression will be used to compute the adjusted odds ratio and 95% CI for the binary outcome–HIV testing. The successful uptake of HIV testing can be dependent on the environment in the HCF so that HIV testing among MSM participants at the same HCF may be corrected or “clustered.” To account for the potential post-randomization clustering effect in this individually randomized clinical trial, a generalized linear mixed-effects model with a logit link function will be fitted, and this model includes both HCF cluster-level and MSM individual-level factors. Structural equation modeling will be performed to evaluate the association between the multilevel intervention and uptake of HIV testing while simultaneously assessing the mediation role of intersectional stigma. We will also perform the same analyses for HIV testing within three months of randomization, although the analyses may be underpowered. The likelihood of intervention contamination across the study groups could not be excluded, because some participants may not receive the respective interventions to which they are randomized, e.g., some members of the control group may seek health care at the intervention HCFs during this trial. Therefore, we will also perform per-protocol analysis, which includes only those participants who strictly adhere to the protocol and report the results along with the results of the intention-to-treat analyses. To estimate the effect size of the HP+ intervention for staff, we will compare the rates of willingness to provide healthcare to MSM between the staff in intervention and control HCFs. Chi-square test and t-test will be used for the binary (willingness) and continuous (stigma score) outcomes, respectively. Multivariate logistic or linear regression models will be fitted while adjusting for confounding factors such as sex and job title of the staff.

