#### Outcomes

For MSM, we will assess important baseline characteristics for describing the sample, including: age, income, gender, education, ethnicity, relationship status, religion, sexual identity, sexual practices, HIV knowledge, HIV testing readiness, HIV testing history and histories of experiencing intersecting stigmas, access and utilization of health and social services, civic engagement and neighborhood. For HCF staff, we will assess a more limited set of baseline characteristics. Our primary outcome will be an uptake of HIV testing within six months of randomization. We will also record the frequency of HIV testing within six months, but we anticipate that few participants will take more than 1 test in this short period. Our secondary outcome will be a reduction in intersectional stigma, both at the HCF-level and among MSM participants. For HCFs, we will construct a latent variable of intersectional stigma using items from questionnaires that measure HIV stigma and discrimination and LGBT stigma among health facility staff. For intersectional stigma among MSM, we will also create a latent variable that is drawn from three scales that measure HIV stigma, same-sex stigma, and gender non-conforming stigma. Outcomes will be assessed within 3-and 6-months post-intervention for HCFs and 3- and 6-months post-intervention for MSM.

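### Baseline imbalance is handled by a post-randomisation equivalence check leading to difference in differences, which is data-driven, poorly matched to its purpose and less precise than prespecified adjustment

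*Protocol article*

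**What the plan says.** All of the analysis text is in the Statistical analysis plan section of the protocol article.

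- The trigger: "First, we will compare baseline data to see if randomization made the groups equivalent". No test, threshold or list of variables defines equivalence.
- The consequence: "If we determine non-equivalence, then the non-equivalent variables will be accounted for in the final analyses using a difference in differences analytic technique". The sentence goes on to refer to randomisation as protection against perceived bias in site selection.
- The primary test, in the same paragraph: "we will use an uncorrected chi-square statistic". It has no baseline term and no covariates.
- Two further models, neither conditional on the check: "multivariable logistic regression will be used to compute the adjusted odds ratio and 95% CI for the binary outcome", and a logit mixed model of which the plan says "this model includes both HCF cluster-level and MSM individual-level factors". No MSM covariates are named for either. Only the staff analysis names any (sex and job title).

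The Outcomes section defines the endpoint: "Our primary outcome will be an uptake of HIV testing within six months of randomization". Its list of MSM baseline characteristics includes "HIV testing readiness, HIV testing history and histories of experiencing intersecting stigmas", with no look-back window for testing history. Under Step 8 (Test), HCF pairs are formed within each city, and the recruitment section sets enrolment at 108 MSM in each of the two regions.

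**The concern.** There are three difficulties.

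1. **The trigger.** If randomisation was done properly, baseline differences are chance. A check on them says nothing about whether the comparison is valid. It only lets chance choose the estimator, and without a threshold it also leaves room for judgement after the data are seen.
2. **The remedy.** The stated purpose is to account for the variables found to differ. Basic difference in differences subtracts the baseline value of the outcome and has no term for age, religion or income. It also needs a baseline counterpart of six-month testing, which the baseline list does not define.
3. **The fit with the primary test.** A chi-square on follow-up testing can carry neither a baseline difference nor a covariate. If the check is triggered, a reader cannot tell whether the chi-square still stands as the primary result.

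At stake are the precision and predictability of the estimate that Aim 2 needs for planning a definitive trial.

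**Working it through.** The plan states no figure on this point, so there is none to reproduce. The inputs are 86 MSM per arm at six months and a 40% control rate (Sample size section). The baseline-to-follow-up correlation of testing (rho) is not given and is assumed over a range.

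**How easily the check could be triggered.** The Outcomes section lists 16 MSM characteristics. Gender is essentially fixed by eligibility, which leaves 15. If each were tested independently at 5% (both assumptions), the chance of at least one flag under perfect randomisation is 1 − 0.95^15 = 0.54. With 10 variables it is 0.40 and with 20 it is 0.64.

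**Precision.** With equal variances at the two times, the variance of the effect estimate relative to no adjustment is:

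- difference in differences: 2(1 − rho)
- adjustment for baseline testing: 1 − rho²
- ratio of the two: 2(1 − rho)/(1 − rho²) = 2/(1 + rho)

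| rho (assumed) | Difference in differences | Baseline adjustment | Ratio | Interval width ratio (square root) |
|---|---|---|---|---|
| 0 | 2.00 | 1.00 | 2.00 | 1.41 |
| 0.3 | 1.40 | 0.91 | 1.54 | 1.24 |
| 0.5 | 1.00 | 0.75 | 1.33 | 1.15 |
| 0.7 | 0.60 | 0.51 | 1.18 | 1.08 |
| 0.8 | 0.40 | 0.36 | 1.11 | 1.05 |

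The ratio exceeds 1 at every rho below 1. Difference in differences does worse than no adjustment when 2(1 − rho) > 1, that is, when rho < 0.5.

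A simulation with binary testing at both times (86 per arm, 4,000 replicates, no clustering, risk-difference scale, one prognostic covariate, six scenarios) agrees. The standard error was 0.081–0.103 for difference in differences, 0.074–0.077 unadjusted, 0.068–0.075 adjusting for baseline testing, and 0.068–0.072 adjusting for baseline testing and the covariate.

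**Does it account for the imbalanced variable?** This uses the same simulation with a covariate imbalance of 0.3 SD and no true effect. The entries are the error left in the risk difference.

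| Covariate's effect on baseline testing, relative to follow-up | Unadjusted | Difference in differences | Adjusted for baseline testing only | Adjusted for baseline testing and the covariate |
|---|---|---|---|---|
| none | +0.047 | +0.047 | +0.047 | +0.001 |
| half | +0.045 | +0.021 | +0.040 | +0.001 |
| equal | +0.046 | +0.002 | +0.035 | +0.001 |

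Difference in differences does what the rule promises only in the last row. Naming the covariate in the model does so in all three.

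**Type I error.** A null simulation (86 per arm, 40% rate, no clustering) switched from chi-square to difference in differences when any of 15 independent 5% checks fired. The overall error was 5.8%, 5.6%, about 5.0% and 4.8% at rho 0, 0.3, 0.5 and 0.7, against about 5.1% for chi-square alone. When baseline testing itself was flagged, in about 5% of trials, the error of difference in differences was 33%, 25%, 18% and 14%.

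**The case against.** The strongest reply is that adjustment does not depend on the check. The plan has an adjusted logistic model and a mixed logit model with individual-level factors in any case, and the choice of their covariates can be left to an SAP that is not shown. This stands. A reader might infer that testing history and city are adjusted for only if they look imbalanced, but the documents do not support that. What remains is that no MSM covariate is fixed in this text, while the one rule it does state about imbalance points elsewhere.

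Second, a regression form of difference in differences can include covariates, and the wording does not exclude it. So it would be too strong to say that the technique cannot adjust for imbalanced variables. Even the basic form removes imbalance that acts equally at both times, and in that case it does better than adjusting for baseline testing alone (+0.002 against +0.035).

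Third, a reader might infer that the pretest seriously inflates the error rate. Under the assumptions tried, the overall rate stays between 4.8% and 5.8%. The distortion is confined to the few trials in which baseline testing is itself flagged.

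Fourth, the rule sits under intervention outcomes in general. Stigma is measured at baseline, 3 and 6 months, so difference in differences has a natural baseline there. The criticism is therefore limited to HIV testing.

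Finally, the 54% trigger rate assumes a test and a threshold that the plan does not state. It illustrates how readily such a rule could fire and is not a property of the plan.

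**Conclusion.** The concern holds for HIV testing in this form: the only stated rule for baseline imbalance is data-driven, has no threshold, and names a technique that in its basic form meets its purpose only when covariates act equally on baseline and follow-up testing. The variance penalty against prespecified adjustment for baseline testing is 2/(1 + rho), or 54%, 33% and 11% at assumed correlations of 0.3, 0.5 and 0.8. That it is less precise at every rho below 1 does not depend on which value is true. It does rest on equal variances at the two times and ignores clustering. Whether difference in differences also loses to no adjustment depends on rho being below 0.5, which the documents do not settle.

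The text also leaves open which result is primary once the check is triggered. It does not show that the chi-square would be replaced, so the fault is ambiguity and not a demonstrated switch. The change should be made because it is nearly free. The case rests on precision and clarity, not on gross error inflation.

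**What to change.** 1. For HIV testing, delete the equivalence check as a trigger and delete the difference-in-differences rule. Keep the baseline table as description only.
2. In the mixed logit model already planned, adjust in all cases for baseline HIV testing history, with a defined look-back such as the six months before baseline, and for city, because HCF pairs are formed within city. Any further covariate believed to predict testing should be named before outcome data are seen, since adjusting for baseline testing alone does not remove imbalance in other variables.
3. Report the unadjusted estimate alongside, and say in one sentence how the chi-square and the mixed-model result rank, so that no baseline comparison can change the ranking.

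The cost is wording, plus one decision. Region is fixed at recruitment and testing history is already on the baseline list, but its look-back is not stated, so the baseline survey item has to be defined to match.
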